### 2.6. Data Management

The collection and storage of data will adhere to the standard requirements of the Data Protection Act 2018. Data will be entered onto electronic spreadsheets, which will be stored on a secure university server using Microsoft OneDrive. All data will be treated confidentially and anonymized for evaluation. Hard copies of data and documents will be kept in a locked and secure filing cabinet for the duration of the study. Following completion of the study, data will be transferred to the University of Central Lancashire Research Data Archive (CLOK), where it will be kept for 5 years. Hard copies will be disposed of confidentially and electronic data deleted after this period of time.

### 2.7. Statistical Analysis

All experimental data (with the exception of the subjective ratings of trial arm allocation) will be continuous and will therefore be presented as mean and 95% CIs. Statistical analysis of all baseline variables will be conducted to compare the three groups at baseline using linear mixed models, with groups modelled as a fixed factor and random intercepts by participants. All analyses of the intervention-based data will be performed using an intention to treat basis, and all randomized participants will be included in the final analysis as far as data collected will allow. Furthermore, in order to determine the effects of the intervention on all of the outcome measures, differences between the three groups will be examined using linear mixed models with group modelled as a fixed factor and random intercepts by participants adopted, adjusted for baseline values modelled as a continuous fixed covariate. For linear mixed models the mean difference (*b*), *t*-value and 95% confidence intervals of the difference will be presented. Finally, blinding efficacy will also be examined using a chi-squared (*Χ*^2^) test. All analyses were conducted using SPSS v27 (IBM, SPSS), and statistical significance for all analyses was accepted as the *p* ≤ 0.05 level.

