## Abstract

Cardiometabolic disease is recognized as the predominant cause of global mortality and healthcare expenditure. Whilst pharmaceutical interventions are effective in the short term, their long-term efficacy remain equivocal and their associated side-effects are concerning. Owing to their high levels of anthocyanins, Montmorency tart cherries and blueberries have been cited as potentially important natural treatment/preventative modalities for cardiometabolic disease. This study proposed a randomized controlled trial, aims to test the effects of consumption of Montmorency tart cherry and blueberry juice on cardiometabolic outcomes compared to placebo. This 20-day, parallel, single-blind, randomized, placebo-controlled trial will recruit 45 individuals, who will be assigned to receive 60 mL per day of either Montmorency tart cherry juice, blueberry juice or a cherry/blueberry flavoured placebo. The primary study outcome is the between-group difference in systolic blood pressure from baseline to post-intervention. Secondary outcome measures will be between-group differences in anthropometric, energy expenditure and substrate oxidation (during rest and physical activity), haematological, blood pressure/resting heart rate, psychological wellbeing and sleep efficacy indices. Statistical analysis will be conducted on an intention-to-treat basis. This study has been granted ethical approval by the University of Central Lancashire, Health Research Ethics Committee (ref: HEALTH 0016) and formally registered as a trial. Dissemination of the study findings from this investigation will be through publication in a leading peer-reviewed journal.

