#### 2.2.3. Sample Size

Power calculations were performed for the primary outcome variable, i.e., the between groups difference in systolic blood pressure. This showed that a total sample size of 45 will be necessary to provide 80% power to detect a minimally important clinical difference (MCID) of 6 mmHg between groups [40], with a projected standard deviation of 5.5 mmHg in each group [41], accounting for a loss to follow up rate of 10%.

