### 2.4. Dietary Intervention

After the conclusion of their baseline data collection session, participants will be provided with either Montmorency tart cherry, blueberry or placebo concentrate. Participants will be required to consume 30 mL of supplement diluted in 100 mL of water twice daily: once in the morning and again in the evening [27]. All supplementations will be kept refrigerated throughout. According to the manufacturer (ActiveEdge, Hanwell, UK), a 30 mL dose of Montmorency tart cherry concentrate (energy: 102 kcal, carbohydrates: 25 g of which sugars: 18 g, protein: 1.10 g and fibre: 2.6 g) is equivalent to approximately 320 mg of anthocyanins. Similarly, taking into account the manufacturers (ActiveEdge, Hanwell, UK) guidelines, a 30 mL dose of blueberry concentrate (energy: 103 kcal, carbohydrates: 22 g of which sugars: 22 g, protein: 0.2 g and fibre: 0.2 g) is equivalent to approximately 387 mg of anthocyanins. Preparation of the placebo will involve mixing 100% un-flavoured maltodextrin carbs (MyProtein, Cheshire, UK) into drinking water using a magnetic stirrer (Stuart Scientific, UK) and stir bar (Fisher Scientific, Waltham, MA, USA). Then, 666 g of maltodextrin will be added to water to create a litre of placebo concentrate, working out as 20 g of maltodextrin per 30 mL serving, closely matching the Montmorency tart cherry or blueberry concentrates. Even amounts of red and black food colouring will be added to match the colour of the Montmorency tart cherry concentrate and even amount of red, blue and black colouring to match the colour of the blueberry supplement. Either cherry or blueberry flavdrops (1 mL) (MyProtein, UK) will then added to match the required flavour. A 30 mL dose of placebo concentrate (100 kcal, carbohydrates 25 g of which sugars: 0 g, protein: 0 g and fibre 0 g) contains 0 mg of anthocyanins. This method of placebo preparation has been shown by previous intervention trials to provide an effective blinding strategy [42].

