Throughout the study, the participants will be encouraged to maintain their habitual diet and exercise routines and asked to refrain from consuming any multivitamin or antioxidant supplements [24]. For their post-intervention data collection session, all participants will be asked to return any un-used supplementation to the laboratory in order to determine the actual amount of supplement/placebo that was consumed (mL), and the % compliance in each group will be reported. Furthermore, in order to examine blinding efficacy, each participant will be asked which trial arm they felt that they had been allocated to at the conclusion of their post-intervention data collection session. In both groups loss to follow up will be monitored, as will be any adverse events.

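### A chi-squared test of true arm by guessed arm mixes flavour recognition with active-versus-placebo unblinding, so it can signal broken blinding when juice and placebo are well masked

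*Protocol article*

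**What the plan says.** The Abstract describes three arms: tart cherry juice, blueberry juice and "a cherry/blueberry flavoured placebo". Section 2.4 explains how the placebo is made. Colouring is added to resemble one juice or the other, and "Either cherry or blueberry flavdrops (1 mL) (MyProtein, UK) will then added to match the required flavour". So one placebo arm contains two products, each built to resemble one of the juices. The article does not give the split between them.

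Also in section 2.4, at the final visit "each participant will be asked which trial arm they felt that they had been allocated to". The question is put in terms of arms, of which there are three.

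Section 2.7 states that "blinding efficacy will also be examined using a chi-squared" test, and that "statistical significance for all analyses was accepted as the" p ≤ 0.05 level. It does not give the layout of the table, and neither section mentions flavour in connection with this test.

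**The concern.** A flavour-matched placebo is meant to hide whether a cherry drink is juice or placebo, and likewise for a blueberry drink. It is not designed to hide cherry from blueberry. The question asked and the test named address a different hypothesis: whether the guessed arm is associated with the true arm in any way. Cherry-juice participants who recognise cherry will rarely guess blueberry, and the reverse, so the two juice rows of the table differ even if nobody can tell juice from placebo.

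The risk is a misread blinding check. A significant result could mean only that the cherry drink tastes of cherry, and the p-value alone would not separate that from a real active/placebo leak. The trial is single-blind with self-reported sleep and wellbeing outcomes (sections 2.1 and 2.5.6), so readers will look at this check.

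**Working it through.** **Inputs from the Protocol article.** Total 45 in three arms (Abstract, section 2.2.3); 10% loss to follow-up (section 2.2.3); significance level 0.05 (section 2.7).

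**The article's own figure.** It gives no number for the blinding test; only the sample size bears on it. For 6 mmHg, SD 5.5, 80% power and two-sided 0.05, n per arm = 2 × (1.960 + 0.842)² × 5.5² / 6² = 13.19. Then 3 × 13.19 / 0.9 = 44, close to the stated 45. I therefore use 45 / 3 = 15 per arm, and 13 per arm after losses (45 × 0.9 / 3 = 13.5).

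**Assumptions not in the article.** Equal allocation; placebo flavours split about evenly (8/7 at 15 per arm, 7/6 at 13); a share p of every arm guesses active whatever they received, which means perfect active/placebo masking; those who guess active name the fruit they tasted with probability r. Here r = 50% means flavour gives no information and r = 100% means it is always recognised.

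**Expected table** with n per arm (columns: guess cherry, guess blueberry, guess placebo):

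- Cherry juice: n × [pr, p(1 − r), 1 − p]
- Blueberry juice: n × [p(1 − r), pr, 1 − p]
- Placebo, even flavour split: n × [p/2, p/2, 1 − p]

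Under independence every row would be n × [p/2, p/2, 1 − p]. Only four cells depart from this, each by np(r − ½), so the chi-squared of the expected table is

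4 × [np(r − ½)]² / (np/2) = 8np(r − ½)², on 4 df.

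With n = 15, p = ½ and r = 1 this is 8 × 15 × 0.5 × 0.25 = 15.0, p-value 0.0047. With p = 1/3 it is 10.0 (p-value 0.040), and with p = 2/3 it is 20.0 (p-value 0.0005). All of this comes from flavour.

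**Simulated rejection at 0.05 of the 3×3 Pearson test, active/placebo masking perfect:**

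| Share guessing active | n per arm | r = 100% | 90% | 80% | 70% |
|---|---|---|---|---|---|
| one third | 15 | 78% | 46% | 25% | 12% |
| one half | 15 | 99% | 74% | 41% | 18% |
| two thirds | 15 | 100% | 90% | 56% | 25% |
| one half | 13 | 97% | 63% | 33% | 16% |

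At r = 50% the same 3×3 test rejects in about 5% of trials. The excess in the table is therefore due to flavour.

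**Another layout that keeps the three-way guess.** Comparing the overall number correct with one-third chance, under full recognition and 15 per arm, rejects in 32%, 62%, 87% and 98% of trials when 1/3, 1/2, 2/3 and 0.8 guess active. With flavour uninformative it rejects in 2% to 4%.

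**After the change.** Merging the two juice guesses into one active category gives 4% to 7% rejection for the 2×2 table of true by guessed active/placebo status, and 4% to 6% for a flavour-stratified (Mantel-Haenszel type) test. This holds at every p and every degree of recognition tried.

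**The case against.** The strongest objection is that the article never fixes the table. An active-versus-placebo chi-squared test fits the wording of section 2.7 and holds its level, and the layout of a supporting check is detail that a journal article may leave to a fuller document. This stands to the extent that one cannot say the trial will declare blinding broken. It does not remove the point: the guess is collected by arm, nothing in sections 2.4 or 2.7 mentions merging guesses or using flavour, and the natural table answers the wrong question.

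The size also rests on assumed recognition and guessing rates. At 70% to 80% recognition with half guessing active, most trials would not reject.

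A reader might infer four stronger things that the article does not support:

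- **That expected counts are too small for the chi-squared approximation.** With n = 15 and p = ½, six of the nine expected counts are 15 × 0.5 / 2 = 3.75, yet the 3×3 test rejects in about 5% of trials when flavour is uninformative. The approximation is adequate here.
- **That a real active/placebo leak could not be separated from flavour.** The guesses already contain the answer. If 80% of juice and 40% of placebo participants guess active and flavour is always recognised, the merged 2×2 table detects the leak in 78% of trials.
- **That the primary result is undermined.** The blinding test enters no efficacy model in section 2.7, and systolic pressure is read by an automated monitor (section 2.5.5).
- **That recognising the fruit is never unblinding.** Section 1.2 also states a hypothesis about the two juices against each other. For that comparison, knowing the fruit is partial unblinding, and the three-arm table would rightly show it.

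**Conclusion.** The point holds as a mismatch between the blinding check and the masking that the placebo is designed to give. On the natural reading, with perfect active/placebo masking, the false-signal rate is about 18% to 99% over 70% to 100% flavour recognition when half guess active, and about 12% to 100% when one third to two thirds do. The nominal rate is 5%. These figures depend on equal arms of 15, a near-even placebo flavour split and the guessing model above, none of which the article states. With 13 per arm they fall slightly. What is at stake is how the blinding check is interpreted, not the estimate or test of the primary outcome. It is worth correcting because the correction is simple and one part of it, the placebo flavour record, has to be made while the trial runs.

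**What to change.** In section 2.7, state that each guess will be coded as active or placebo and compared with true active/placebo status. Preferably do this within flavour: cherry juice against cherry placebo, blueberry juice against blueberry placebo, combined by a flavour-stratified test. Report the proportion guessing correctly with its 95% CI, or a blinding index. An exact test may be chosen for the small strata but is not essential.

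Record which flavour each placebo participant received. The merged active/placebo comparison does not need this, but the within-flavour comparison does.

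Keep the three-arm cross-tabulation as a descriptive display, since fruit recognition bears on the juice-versus-juice comparison.

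The cost is a change of analysis wording, one recorded variable and slightly more analysis, with no extra visits or questions. The drawback is that within-flavour placebo groups would be only about 7 or 8, so those estimates will be imprecise.

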## 3. Ethics and Dissemination

This study has been granted ethical approval by the University of Central Lancashire Health Research Ethics Committee (ref: HEALTH 0016) and formally registered as a trial (NCT04177238). Any required alterations to the experimental protocol will be sent for re-review/approval by the research ethics committee and amended at the trial registry. Participants who express a desire to see a summary of the trial findings will be provided with such information when the data have been analysed. Dissemination of the study findings from this investigation will be through publication in a leading peer-reviewed journal, and presentation at both national and international scientific conferences.

## 4. Conclusions and Limitations

The placebo randomized trial described in this protocol paper will explore the effects of both Montmorency tart cherry and blueberry juice on the primary and secondary outcomes pertinent to the aetiology of cardiometabolic disease and its comorbidities. As cardiometabolic conditions, they are recognized as the predominant causes of global mortality and healthcare expenditure, and the findings may provide important clinical information regarding the potential prophylactic role that anthocyanin rich fruit supplementation may play in healthy individuals.

However, like all research, the trial protocol described in this paper is not without limitations. Firstly, in order to minimize both inter and intra-subject variability, the proposed protocol will involve examining participants after an overnight fast. Therefore, it is possible that data collection will not capture the peak vasomodulatory effects of the experimental supplementation. Importantly, participants will be given instructions regarding storage/intake, and compliance to each intervention group will be quantified as any un-used supplementation will be returned and measured. However, it is ultimately not possible to control for or determine how participants actually stored or when chronologically they consumed their supplementation. Furthermore, although blood pressure will be quantified using established techniques in accordance with the European Society of Hypertension, measures will be obtained at a single time point in a laboratory environment. Therefore, 24 h continuous blood pressure monitoring may be more efficacious and representative of normal daily-living conditions and whilst also negating the potential effects of white-coat hypertension. Finally, it has been speculated that the positive effects of anthocyanin rich supplementation such as Montmorency tart cherries or blueberries on cardiometabolic health are mediated via anti-inflammatory, antioxidant and nitric oxide promoting effects. However, owing to time and cost implications, the proposed investigation will not examine pathophysiological biomarkers, meaning that the mechanistic bases for any improvements in cardiometabolic parameters will not be elucidated. Improved understanding of the mechanistic influence of anthocyanin rich supplementation on cardiovascular and metabolic health makes the expectation tenable that they can be better exploited in order to improve cardiometabolic health throughout lifespans. Therefore, future investigations beyond the study protocol described here should seek to explore and utilize the mechanistic pathways of Montmorency tart cherry and blueberry supplementation.

## Figures and Tables

**Figure 1 ijerph-18-09759-f001:**
[figure not shown]
Consort diagram showing the study design.
